## 8.12 Discharge

At discharge, the investigator or delegated staff registers the date and time of discharge and any ongoing adverse events.

## 8.13 Suspension or termination of the clinical investigation

In case of a safety concern from any of the participating centers that is confirmed by the safety board, the study might be suspended or terminated by the safety board.

# 9 Adverse events

## 9.1 Adverse event definition and reporting

An AE is any untoward medical occurrence, unintended disease or injury of any untoward clinical signs (including an abnormal laboratory finding) in subjects, users or other persons, in the context of a clinical investigation, whether or not related to the investigational medical device.

This definition includes

- a. Events that are anticipated as well as unanticipated.
- b. Events occurring in the context of a clinical investigation related to the investigational device, the comparator or the procedures involved.

For the purpose of this protocol, an AE will be defined as any adverse medical change (i.e., de novo or increased severity in a preexisting condition) from the subject's baseline condition, that occurs during the course of the clinical study, whether considered device-related or not and meeting the protocol reporting requirements.

AE reporting requirement applies to both the test group (PrimECC®) and control group (standard crystalloid priming solution). AEs will be collected from the induction of anesthesia until the last subject's last study visit. Ongoing AEs at subject's last study visit at postoperative day 4, will be followed up until discharge from hospital.

Symptoms caused by the surgical procedure are expected to occur. The following are examples of unavoidable events caused by the surgical procedure are not considered AEs:

- Anesthesia related nausea/vomiting
- Vocal cord dysfunctions
- Low grade fever (less than 38 °C) secondary to chest tube presence.
- Incision pain, redness, and inflammation.
- Shortness of breath not meeting respiratory failure definition
- Post-operative procedure complications
- Mild to moderate bruising at the surgical site
- Back pain related to operating room table
- Sleep issues (insomnia)
- Gastrointestinal discomfort (i.e., constipation, decreased appetite, diarrhea)
- Pulmonary observations (i.e., wheezing, cough)
- Cardiovascular observations (i.e., phlebitis, arrhythmias, cold extremities)
- Neurological observations (i.e., hallucinations, confusion)
- Urological observations (i.e., urinary tract infection, urinary retention)
- There may be additional unavoidable events not listed which can be documented in the source by the investigator.

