### Precautions

PrimECC® is ready to use, no additives are necessary.

The responsibility for correct clinical use and technique rests with the user. The Instructions for Use is only provided as a suggestion for procedure, the user must on the basis of her or his medical training and experience evaluate the suitability of this procedure.

PrimECC® must not be used for fluid therapy pre- or postoperatively. The maximum dosage of 1.5 g dextran 40 per kg body weight must not be exceeded (= 33 ml PrimECC®/kg body weight).

PrimECC® contains lactate which may slightly increase plasma lactate levels (by about 6 mmol/l).

Unfractionated heparin should be used cautiously post-operatively as the interaction with dextran might result in excessive bleeding.

**Pregnancy:** There are no data on the use of PrimECC® during pregnancy. PrimECC® should only be administered to pregnant women if strictly needed.

**Lactation:** It is not known to what extent PrimECC® passes into breast milk. In the absence of human data, breastfeeding may be continued if clearly needed considering the benefit of breast feeding for the child and the benefit of therapy for the woman.

**Treatment of children:** There are no data on the use of PrimECC® on children. PrimECC® should only be administered to children if strictly needed.

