### 6.3 Secondary objective

The secondary objectives are to study the safety parameters when PrimeECC® is used in a large cohort of patients, especially related to bleeding and anaphylactic events, and to assess renal, and myocardial injury.

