### 11.6 Safety

The assessment of safety will be based primarily on the frequency of adverse events and laboratory abnormalities and on percentage of subjects with adverse events and laboratory abnormalities. Other safety data will be summarized as appropriate. Laboratory data will be summarized by presenting shift tables using extended normal ranges (baseline to most extreme post-baseline value), by presenting summary statistics of raw data and change from baseline values (mean, medians, standard deviations, ranges).

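### Section 9.1 lets undefined post-operative complications, bleeding among them, be left out of adverse event reporting at the investigator's discretion

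*Protocol*

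**What the plan says.** Protocol section 9.1 opens with a wide definition of an AE. It includes "Events that are anticipated as well as unanticipated", as well as events related to the device, the comparator or the procedures. The trial-specific definition that follows covers any adverse change from baseline, "whether considered device-related or not and meeting the protocol reporting requirements".

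The section then sets out a list of exceptions. Its lead-in reads "The following are examples of unavoidable events caused by the surgical procedure are not considered AEs". Among the items is "Post-operative procedure complications", with no definition. Arrhythmias, confusion and urinary tract infection also appear without a severity limit. The last item is open: "There may be additional unavoidable events not listed which can be documented in the source by the investigator".

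Two other sections give this weight. Section 6.3 makes safety a secondary objective, "especially related to bleeding and anaphylactic events". Section 11.6 states: "The assessment of safety will be based primarily on the frequency of adverse events and laboratory abnormalities". The Precautions in section 5.5 add, for post-operative unfractionated heparin, that "the interaction with dextran might result in excessive bleeding".

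**The concern.** On its ordinary meaning, a post-operative bleed, a tamponade or a return to theatre is a complication of the operation. A site that reads the list this way can treat such an event as not an AE. It then need not enter the AE form that carries severity, seriousness and relatedness. Another site can read the broad definition and record the same event.

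AE frequencies would then depend partly on local habit. A difference in bleeding events between the arms would be harder to see in the AE tables, in a trial whose safety objective singles out bleeding. AE definitions belong in the protocol, so this is not a matter to leave to the statistical analysis plan.

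**Working it through.** The point is textual, so the check is to set the sections side by side.

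1. **Definition against list.** The general definition in 9.1 counts anticipated and procedure-related events. The list then takes out events because surgery is expected to cause them. The trial-specific definition softens the conflict by requiring that reporting requirements be met, but the list is itself part of those requirements and does not say where it stops.

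2. **Limits on neighbouring items.** Fever is excepted only below 38 °C, bruising only up to moderate grade, and breathlessness only short of respiratory failure. The complications item has no such limit, so nothing separates a trivial event from a major one.

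3. **Meaning of procedure.** Section 9.8 restricts the word to priming and use of the ECC and sets the rest of the surgery apart. Section 9.1 uses it for the surgery. Read with the 9.8 meaning, the item would except the very events that 9.8 wants assessed. Read with the ordinary meaning, it excepts surgical complications, bleeding included.

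4. **What depends on AE status.** Section 9.7 asks for severity, relationship and seriousness for reportable AEs. Section 9.12 has sites report a serious adverse event (SAE) by completing the AE form and marking it serious. Section 9.8 classes events whose relatedness cannot be assessed as possibly related, but an event that is not an AE never reaches that step.

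5. **Overrides.** Section 9.3 states expressly that acute kidney injury needing dialysis or continuous renal replacement therapy (CRRT) is reported as an AE or SAE. No equivalent sentence exists for bleeding, or for listed events that turn out to be serious.

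6. **Urinary tract infection.** Section 9.10 counts an infection treated with systemic antibiotics and with a positive urine culture as significant, unless it was present at baseline or is nosocomial. Section 9.1 lists urinary tract infection as not an AE. Such an infection would be registered under 8.11 and still be absent from the AE counts.

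**Illustration of what under-recording can do.** The protocol gives no bleeding rates, so the rates here are assumptions. With 1:1 allocation (also assumed), 366 / 2 = 183 per arm. At the planned 50% versus 35%, the two-sided Fisher exact test then has 80.3% power, which agrees with section 6.10. Now take true bleeding-event rates of 10% and 20%, with a fraction s of events recorded as AEs in both arms:

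| s | Recorded rates | Difference, percentage points | Exact Fisher power |
|---|---|---|---|
| 1.00 | 10% v 20% | 10 | 73% |
| 0.75 | 7.5% v 15% | 7.5 | 56% |
| 0.50 | 5% v 10% | 5 | 37% |
| 0.25 | 2.5% v 5% | 2.5 | 16% |

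The ratio stays at 2 throughout, while the difference shrinks in proportion to s. The table shows the mechanism. It does not estimate what will happen in this trial.

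**The case against.** The strongest reply is that bleeding appears nowhere in the list. The lead-in confines the list to events that surgery makes inevitable, and a tamponade or reoperation is not obviously inevitable. This stands as far as it goes: the text permits exclusion and does not order it. It does not settle the matter, because the item has no definition and the final bullet invites additions.

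Second, bleeding is measured in every subject without any AE judgement. Section 6.9 lists drain loss over 24 hours, transfusions, hemostatic drugs, platelets, INR and APTT. Sections 8.10 and 8.11 add bleeding volume and reoperation for bleeding, and 11.4 names bleeding and coagulation as safety variables. Laboratory abnormalities are also part of the main basis in 11.6. This stands, and it limits the harm considerably. These measures do not, however, carry seriousness or causality.

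Third, 9.12 requires every SAE to be reported whatever its perceived relationship, 9.7 requires all deaths to be reported, and neither exempts the 9.1 list. It therefore cannot be said that expedited reporting is lost. What is missing is a sentence saying which rule prevails.

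Fourth, the Precautions concern heparin given after surgery, and bleeding from that interaction is not caused by the operation, so the list strictly does not reach it. That is right in principle. But a blinded investigator has to decide the cause of a bleed without knowing the priming solution, so the distinction is hard to apply.

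**Conclusion.** The point holds as a contradiction within 9.1 that leaves AE ascertainment to discretion. Post-operative bleeding and other complications can drop out of the AE-based part of the safety assessment, with their severity, seriousness and relatedness, and differently by site.

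A reader might infer that bleeding and the other target harms are taken out of the safety analysis altogether. The documents do not support that. Bleeding is captured by separate measures. Anaphylaxis is an anticipated device effect under 7.1.2, not a surgical event. Dialysis-requiring kidney injury is expressly reportable. Nor does the listing of confusion remove a central nervous system outcome, since those outcomes in 6.8 are biomarkers.

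The size cannot be computed from the protocol, because it depends on bleeding-event rates and on how sites read the list. The primary endpoint, the sample size of 366 and the efficacy analyses are untouched. The power figures rest on assumed rates and on equal under-recording in both arms. The wording should be corrected, but it does not threaten the trial's main result.

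**What to change.** Delete the complications item and the final open-ended item from the list in 9.1. Add a sentence that the list never applies to an event that meets the seriousness criteria in 9.3, is possibly related to the device or the ECC procedure, or is a bleeding complication. State that such events are recorded as AE or SAE in the eCRF in both arms. The sponsor should also say how a bleeding complication is told apart from expected drainage.

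Then reconcile the related sections:

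- **9.8:** it says that surgical complications unrelated to ECC are not assessed for relatedness. It must be clear how a newly recorded bleed is handled, and procedure needs one meaning in 9.1 and 9.8.
- **9.10:** align the urinary tract infection item with the definition of significant infection.
- **9.12:** confirm that SAE reporting prevails over the list.

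The override should not extend to every renal event. At the planned rates, 183 × 0.50 + 183 × 0.35 = 155.6, so about 156 primary-endpoint events would be duplicated as AEs. Kidney injury not needing dialysis or CRRT is already captured by the primary endpoint. Nor should it cover every event that needs intervention, which would bring back treated nausea and constipation.

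The cost is amendment wording, site retraining and somewhat more AE forms. If recruitment is under way, AE counts before and after the change would not be fully comparable, and the report should say so.

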## 9.2 AE determination

AE determination is based on three levels of evidence. If level 1 can be determined, then level 2 and 3 events may be updated to the highest level of reporting.

Level 1 – final diagnosis

Level 2 – signs

Level 3 – symptoms

Every effort should be made to collect Level 1 evidence of any AE. If an AE has all three levels of evidence, report the AE only once at the highest level of evidence, which is the final diagnosis (Level 1). A single AE should not be reported as multiple AEs based on separate symptoms, signs, and diagnosis.

In any case where a diagnosis is not possible, AE determination should be based on the next highest level of evidence, signs (Level 2), followed by symptoms (Level 3), if only symptoms are available.

A corrective action, itself is not an AE. The AE should always be determined based on the reason that corrective action is taken.

### 9.3 Serious adverse event

A Serious Adverse Event is one that led to anything of the following:

1. death

2. serious deterioration in the health of the subject, that resulted in any of the following

- life-threatening illness or injury,
- permanent impairment of a body structure or a body function,
- hospitalization or prolongation of hospitalization,
- medical or surgical intervention to prevent life-threatening illness or injury, or permanent impairment to a body structure or a body function
- chronic disease
- fetal distress, fetal death or a congenital physical or mental impairment or birth defect

3. A planned hospitalization for a pre-existing condition or a procedure required by this protocol, without a serious deterioration in health, is not considered to be a SAE.

In the study all AKI related events that are requiring any type of intermittent dialysis or continuous renal replacement therapy (CRRT) should be reported as an AE/SAE.

### 9.4 Adverse device effect

An adverse device effect (ADE) is an AE that is related to an investigational medical device. This definition includes any AE resulting from insufficiencies or inadequacies in the instructions for use, the composition, the use, or any malfunction of the investigational medical device. It also includes any event that is a result of a user error or intentional misuse.

### 9.5 Serious adverse device effect

A serious ADE (SADE) is defined as an ADE that has resulted in any of the consequences characteristic of an SAE.

### 9.6 Unanticipated serious adverse device effect (USADE)

A USADE is any serious adverse effect on health or safety, any life-threatening problem or death caused by, or associated with a device, if that effect, problem, or death was not previously identified in nature,

severity, or degree of incidence in the investigational plan (e.g., ICF, Study Protocol, Instructions for Use (IFU), publications, etc.), or any other unanticipated serious problem associated with a device that relates to the rights, safety or welfare of subjects.

### 9.7 Reporting of all adverse events

The signs, symptoms and sequelae of an underlying AE should not be reported as separate AEs. All reportable AEs must be recorded on the CRF in accordance with the protocol AE reporting requirements. All AEs must also be described by duration (start and resolution dates), severity, relationship to the investigational device, comparator and/or procedure, action taken to resolve the event, outcome of the event, and whether it is considered to be serious or not. Additional information, such as procedural notes, treatment notes, or a signed clinical summary, may be required as supporting documentation for the reported AE.

During the study, all deaths must be reported to the Sponsor within 24 hours of the investigator's (or a designated staff person's) knowledge of the death. These also should be reported on the End of Study CRF. A copy of death records, medical records for the events that led to the subject's death, death certificate (if available) and an autopsy report (if performed) must be sent to the Sponsor as soon as they become available.

### 9.8 Relationship of the AE to the study device or study procedure

The sponsor and the investigator will distinguish between the AE related to the investigational device or comparator and those related to the procedure. The procedure in this context is restricted to the pre-operative procedures involving priming of the ECC and the on-going use of ECC during surgery. The procedure does not include the complete surgery and surgical complications not related to the use of ECC should not be assessed for relatedness. Safety events occurring from start of the pre-operative procedures until Postoperative day 4 (96h) could be related to the procedure. The definition of procedure will be the same for both the test group and the control group.

Safety events occurring from start of ECC, when the solution enters the subject's circulation, and until Postoperative day 4 (96h), could be related to the investigational device and comparator and a relationship assessment should be made. An AE can be related both to procedures and the investigational device.

The relationship between the use of the medical device or the procedure and the occurrence of each AE shall be assessed and categorized. During causality assessment activity, clinical judgement shall be used and the relevant documents, such as the Instructions for Use and the Clinical Investigation Plan shall be consulted, as all the foreseeable serious adverse events and the potential risks are listed and assessed there. The presence of confounding factors, such as concomitant medication/treatment, the natural history of the underlying disease, other concurrent illness or risk factors shall also be considered.

For the purpose of harmonizing reports, each AE will be classified according to four different levels of causality, described below.

1. Not related
2. Possible
3. Probable
4. Causal relationship

The sponsor and the investigators will use the following definitions to assess the relationship of the serious adverse event to the investigational device, the comparator or the investigation procedure.

1. **Not related** - Relationship to the investigational device or procedures can be excluded when
  - the event has no temporal relationship with the use of the investigational device, or the procedures related to application of the investigational device;
  - the serious adverse event does not follow a known response pattern to the medical device (if the response pattern is previously known) and is biologically implausible;
  - the discontinuation of medical device application or the reduction of the level of activation/exposure
  - when clinically feasible - and reintroduction of its use (or increase of the level of activation/exposure), do not impact on the serious adverse event;
  - the event involves a body-site or an organ that cannot be affected by the device or procedure;
  - the serious adverse event can be attributed to another cause (e.g., an underlying or concurrent illness/ clinical condition, an effect of another device, drug, treatment or other risk factors);
  - the event does not depend on a false result given by the investigational device used for diagnosis, when applicable;

In order to establish the non-relatedness, not all the criteria listed above might be met at the same time, depending on the type of device/procedures and the serious adverse event.

2. **Possibly related** - The relationship with the use of the investigational device or comparator, or the relationship with procedures, is weak but cannot be ruled out completely. Alternative causes are also possible (e.g., an underlying or concurrent illness/ clinical condition or/and an effect of another device, drug or treatment). Cases where relatedness cannot be assessed, or no information has been obtained should also be classified as possible.
3. **Probably related** - The relationship with the use of the investigational device or comparator, or the relationship with procedures, seems relevant and/or the event cannot be reasonably explained by another cause.
4. **Causal relationship** - The serious adverse event is associated with the investigational device, comparator or with procedures beyond reasonable doubt when:
  - the event is a known side effect of the product category the device belongs to or of similar devices and procedures;
  - the event has a temporal relationship with investigational device use/application or procedures;
  - the event involves a body-site or organ that the investigational device or procedures are applied to; or the investigational device or procedures have an effect on;
  - the serious adverse event follows a known response pattern to the medical device (if the response pattern is previously known);
  - the discontinuation of medical device application (or reduction of the level of activation/exposure) and reintroduction of its use (or increase of the level of activation/exposure), impact on the serious adverse event (when clinically feasible);

- other possible causes (e.g. an underlying or concurrent illness/ clinical condition or/and an effect of another device, drug or treatment) have been adequately ruled out;
- harm to the subject is due to error in use;
- the event depends on a false result given by the investigational device used for diagnosis, when applicable

In order to establish the relatedness, not all the criteria listed above might be met at the same time, depending on the type of device/procedures and the serious adverse event.

### 9.9 Degree of severity

The degree of severity of the AE to the subject's health will be documented on the AE CRF.

1 = Mild- intervention not indicated or limited intervention

2 = Moderate- non-urgent intervention indicated

3 = Severe- urgent intervention, debilitating, life-threatening, requires or prolongs hospitalization, death.

### 9.10 Significant infection

Any significant infection is reported between time of 24h post-ECC and postoperative day 4. This is defined as requiring treatment with systemic antibiotics and a positive urine/blood and/or sputum culture. This excludes infections already present at baseline or considered nosocomial.

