## 8 Schedule of Assessments

A preliminary review of medical records should be performed to assess if a subject will be eligible for participation in the study. This includes medical history, renal status, liver status, heart and lung status and any infectious diagnosis. Investigators or delegated staff are responsible for obtaining informed consent and authorization to use and disclose protected health information before randomization. The study does not require specific screening study procedures other than a medical chart review. A final review of the subject's medications and medical history will be confirmed at time of surgery to make sure that nothing has changed since consenting to the study. The "Acute Kidney injury risk score" will be used to evaluate that the subject fulfil the inclusion criteria at admission the day before surgery. If, for any reason, the surgery is postponed  $\geq 7$  days, a recalculation of AKI score is required with a retaken sample of s-crea.

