## 8.11 Postoperative parameters

In addition to the laboratory analysis defined above, the patient fluid balance is registered as the sum of infusion of crystalloids, colloids, transfusions, bleeding and urine output. All infusions of blood and/or plasma products are recorded during the study period. Reoperation for bleeding, time on ventilator, significant infections, and ICU length of stay and hospital length of stay are registered.

Use of mechanical renal support such as continuous renal replacement therapy (CRRT) or hemodialysis is registered during the study period.

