### 11.2 Patient demographics/ other baseline characteristics

Baseline value is defined as the last non-missing assessment prior to surgery. Summary statistics will be provided by treatment group, both for FAS and PP populations, for demographics and baseline characteristics, including age, sex, weight, height, body mass index (BMI), self-reported ethnicity, diabetes, smoking history, dyspnea, hypertension, ejection fraction (LVEF), time of angiography, operative priority, planned cardiac procedure, peripheral vascular disease, triple vessel disease, eGFR, prior hospitalization, and Euroscore (optional). Continuous variables will be summarized using n, mean, standard deviation, median, Q1, Q3, minimum, and maximum. Categorical variables will be summarized using frequency and percentage.

The p-values will be provided for descriptive purposes and will not be considered to define any formal basis for determining factors to be included in statistical models.

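### Section 9.10 excludes infections considered nosocomial from a largely inpatient window, so the significant-infection count would omit nearly all new infections and depend on how each site uses an undefined word

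*Protocol*

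**What the plan says.** Section 9.10 of the protocol sets the variable up in three steps.

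- Window: "Any significant infection is reported between time of 24h post-ECC and postoperative day 4".
- Case definition: "This is defined as requiring treatment with systemic antibiotics and a positive urine/blood and/or sputum culture".
- Exclusions: "This excludes infections already present at baseline or considered nosocomial".

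The protocol does not define nosocomial, in 9.10 or anywhere else.

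Section 8.11 lists the variable with other recorded items: "Reoperation for bleeding, time on ventilator, significant infections, and ICU length of stay and hospital length of stay are registered". It does not appear among the primary, secondary, exploratory or other pre-specified outcome measures in sections 6.5 to 6.9.

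Three other passages bear on how the exclusions work. Section 8 has eligibility confirmed by checking that subjects "fulfil the inclusion criteria at admission the day before surgery". Section 11.2 fixes baseline: "Baseline value is defined as the last non-missing assessment prior to surgery". Section 9.1 lists unavoidable consequences of surgery that are not counted as AEs. The list includes complications of the procedure after the operation and this item: "Urological observations (i.e., urinary tract infection, urinary retention".

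**The concern.** A subject who enters hospital the day before surgery and develops a new infection on postoperative day 2 has, in the ordinary sense of the word, a hospital-acquired infection. Section 9.10 tells the site to leave it out. An infection that is not new was there at baseline, and 9.10 leaves that out as well. Between them the two exclusions cover almost everything the case definition could pick up.

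Two things are at stake. First, a low count in both arms would follow from the definition and could be misread as evidence that the arms do not differ on infection. Safety in a large cohort is part of the secondary objective (section 6.3), so the variable should be able to show a difference if there is one. Second, the trial is multicentre and the key word is left to local judgement. A site that reads it literally would record almost nothing, while a site that reads it narrowly would record most of its cases. The total would then reflect reading habits as much as infections.

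**Working it through.** The protocol gives no infection rate, expected count or planned comparison for this variable, so there is no figure to reproduce. Its sample size of 366 concerns AKI and plays no part here. The check is to set the passages side by side.

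**Step 1: place the window in the hospital stay.** Admission is the day before surgery (section 8). Exact clock times are not given. Assume that ECC ends about 0.5 to 1.5 days after admission.

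- Window opens, 24 h post-ECC: 0.5 + 1 = 1.5 days to 1.5 + 1 = 2.5 days after admission.
- Window closes, 96 h post-ECC: 0.5 + 4 = 4.5 days to 1.5 + 4 = 5.5 days after admission.

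The subject has therefore been in hospital for well over a day before the first infection can be counted.

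**Step 2: is the subject still in hospital during the window?** The protocol does not say so for every subject, but it implies it for most. Serum creatinine is drawn on postoperative days 2, 3 and 4 (sections 8.7 to 8.9), and section 9.1 has AE follow-up running beyond the last visit: "Ongoing AEs at subject's last study visit at postoperative day 4, will be followed up until discharge from hospital". I therefore call the window largely, not wholly, inpatient.

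**Step 3: sort the infections that meet the antibiotic and culture criteria in the window.**

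| Origin of the infection | Treatment under 9.10 |
|---|---|
| Present at the last assessment before surgery | Excluded as baseline |
| Acquired during the hospital stay | Excluded as nosocomial, on the ordinary meaning |
| Incubating but undetected at baseline | Could count |
| Acquired after a discharge before 96 h | Could count |
| Acquired in hospital, but the investigator does not call it nosocomial | Counts, by local judgement |

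The first two rows take in nearly all cases. The third and fourth should be few. The last has no rule behind it, because the term is undefined.

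**Step 4: does the AE route catch what 9.10 leaves out?**

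- Serious infections: yes. Life-threatening illness or prolonged hospitalization makes an event an SAE (section 9.3), and SAEs are reported whatever their relationship to the product (section 9.12).
- Non-serious infections treated with antibiotics: not reliably. Section 9.1 removes urinary tract infection by name and post-operative procedure complications as a class. A culture-positive, treated urinary infection acquired on the ward can fall outside 9.10 as nosocomial and outside the AE log through the 9.1 list.

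**The case against.** The strongest reply is that little depends on this variable. It is not an endpoint and is not named in the analysis sections (11.3 to 11.6), and safety is judged primarily on adverse events and laboratory abnormalities (section 11.6). AEs are collected from induction of anesthesia, and serious infections reach the sponsor as SAEs whatever 9.10 says. All of this stands, and it limits the weight of the point. It does not repair the definition, and the 9.1 list leaves the gap shown in the last step of the check.

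A second reply is that the wording leaves the matter to the investigator and may have been meant narrowly, for example to remove ward infections unrelated to surgery or ECC. That is possible, but the text does not say it. If it was the intention, sites cannot tell, and the count still depends on local reading.

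A reader might also infer more than the documents support:

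- *That the definition can count nothing at all.* It cannot be put that strongly. A stay to 96 h is not stated for every subject, and some infections escape both exclusions.
- *That the trial is blind to infection.* The SAE route contradicts this.
- *That the product is labelled with a specific infection risk.* The instructions for use in section 5.5 make only a general remark about invasive procedures, and the anticipated device effects in section 7.1.2 are anaphylactic-type reactions.
- *That 9.1 and 9.10 flatly contradict each other.* Section 9.10 does not call a significant infection an AE, and section 8.11 records it as a separate parameter, so both can be followed. The relation is unclear because 9.10 sits in the adverse-event chapter.
- *That starting at 24 h is an error.* Section 9.8 considers device relationship from the start of ECC, so an earlier start could be argued for, but a later one is a defensible choice for this variable.

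**Conclusion.** The point holds as a defect in the definition of one recorded safety parameter. Followed as written, section 9.10 leaves out nearly all new infections in its own window and makes the remainder depend on an undefined term. The conclusion rests on two assumptions: that nosocomial carries its ordinary meaning of hospital-acquired, and that most subjects remain in hospital for most of the window. The protocol supports the second without stating it.

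The size cannot be expressed as a number of cases, because the documents give no infection rate. The consequence is confined to this parameter. The primary endpoint, its test and the sample size are untouched, and serious infections are still captured. What may be lost is the record of treated, non-serious infections, urinary ones above all. The correction is worth making because it is cheap and the present count would not be interpretable.

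**What to change.** In section 9.10, delete the words that exclude infections considered nosocomial and keep the exclusion of infections present at baseline. Add one sentence to reconcile 9.10 with the list in 9.1: an infection meeting the 9.10 definition, including a culture-positive urinary infection treated with systemic antibiotics, is recorded regardless of that list. The reporting window need not change.

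The cost is a short wording amendment and a few more events to record. If subjects have already been recorded under the present text, sites would need to check those records against the amended definition, so that the count means the same thing throughout the trial.
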